#### Inclusion criteria

Patients will be included if they fulfil all the following criteria:Meet the diagnostic criteria of AP [3], which fulfil two of the following three items: typical symptoms and signs of abdominal pain, elevated serum amylase and/or lipase at least three times the upper limit of normal, and AP characteristic image findings.Aged between 18 and 75 years, male or female.Admitted to Pancreatitis Centre Ward within 72 h of disease onset.Written informed consent obtained.

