#### Secondary outcome measurements

I.Secondary outcomes during the index admissionThe occurrence of new-onset of any organ failure (SOFA score for respiratory, cardiovascular, or renal system ≥ 2 points) or new-onset of POF (organ failure lasts > 48 h). New onset is defined as events that occur after randomisation and not present 24 h before randomisation.Cumulative levels of C-reactive protein (CRP) on days 1, 2, 3, 5, 7, 14, 21, and 28 after admission.Levels of albumin, procalcitonin, interleukin-6 (IL-6), and neutrophil count on day 0, day 3, day 5, day 7, and day 14.Daily visual analogue scale (VAS) score of pain [45].Daily Pancreatitis Activity Scoring System (PASS) score within the 1st week after enrolment [46].Duration (days) of Systemic Inflammatory Response Syndrome (SIRS ≥ 2 points) [47].Duration (days) of fasting.The requirement of the anal tube.The requirement of prokinetic agents.Duration (days) of gastrointestinal decompression.Duration (days) of IAH and ACS.The receipt of respiratory support and renal replacement therapy.Length of intensive care unit (ICU) stays.Local pancreatic injury by contrast-enhanced computerised tomography (CECT) on days 7 and 14.Potential safety signals.Length of hospital stay.In-hospital cost.II.Secondary outcomes within 26 weeks after enrolmentThe requirement for catheter drainage or necrosectomy.Infected pancreatic necrosis.All-cause mortality.Self-report health situation by five-level EuroQol five-dimensional (EQ-5D-5L) [48].

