**Table 2 Tab2:**
[figure not shown]
Study schedule of the CAP trial

*CQCQD* chaiqin chengqi decoction, *EQ-5D-5L* five-level EuroQol five-dimensional questionnaire, *CRP* C-reactive protein

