## Assignment of interventions: allocation

### Sequence generation {16a}

After the completion of screening measurements and the acquisition of signed consent, eligible participants will be randomised in a 1:1 ratio to either the treatment or control group. The randomisation code will be automatically created by computer using Analytics Software & Solutions software (SAS, version 9.3, SAS Institute Inc, USA).

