### Plans for collection, laboratory evaluation, and storage of biological specimens for genetic or molecular analysis in this trial/future use {33}

Blood samples of participants will be collected on admission and 1, 3, 5, and 7 days after admission, and the samples will be transferred and handled by professional biobank technicians. Finally, serum, plasma, and white blood cell samples will be stored in West China Biobanks, certified by the China Human Genetic Resources Management Office (No. [2016]406 and No. [2022]BC0040).

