## Statistical methods

### Statistical methods for primary and secondary outcomes {20a}

Data cleaning and statistical analysis will be performed by a statistician blinded to the whole trial process using the latest version of SAS software. The results of the data will be expressed as the means with ranges, medians with interquartile ranges, or numbers of patients with percentages. The comparison between the individualised CQCQD and control group is the primary interest in this study. Continuous variables are compared using the independent-sample *T* test or the Mann–Whitney *U* test (for non-normal distributions). Categorical variables are compared with the chi-squared test or Fisher’s exact test. Statistical tests will be two-sided, and *P* values < 0.05 will be considered significant.

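### The listed CRP series starts on day 1 with no pre-dose value and the stated test is unadjusted, so cumulative CRP is compared less precisely than it could be (minor)

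*Protocol article*

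**What the plan says.** Under Secondary outcome measurements, the protocol article gives the CRP outcome as "Cumulative levels of C-reactive protein (CRP) on days 1, 2, 3, 5, 7, 14, 21, and 28 after admission". The next item in the same list reads "Levels of albumin, procalcitonin, interleukin-6 (IL-6), and neutrophil count on day 0, day 3, day 5, day 7, and day 14". CRP thus has eight listed time points and no day 0, while albumin, procalcitonin, IL-6 and neutrophil count each have a day 0.

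Three other places bear on this:

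- The inclusion criteria allow a variable delay before entry: "Admitted to Pancreatitis Centre Ward within 72 h of disease onset".
- The biological specimens section {33} treats the admission draw as distinct from day 1: "Blood samples of participants will be collected on admission and 1, 3, 5, and 7 days after admission". It adds that "serum, plasma, and white blood cell samples will be stored in West China Biobanks".
- The statistical methods section {20a} states the test for continuous outcomes: "Continuous variables are compared using the independent-sample *T* test or the Mann–Whitney *U* test (for non-normal distributions"). It names no baseline covariate for any marker.

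The participant timeline is in Table 2 ("Study schedule of the CAP trial"). Its body is not available here, but its legend defines CRP, so CRP appears in it.

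**The concern.** A cumulative CRP total depends partly on how inflamed the patient was before any study drug. That starting level will vary, because one patient may arrive a few hours after onset and another after nearly 72 h.

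The first listed CRP is on day 1 after admission. The abstract has patients assessed for enrolment at admission, and the intervention section sets the starting regimen at allocation. For a patient randomised and dosed on the day of admission, the day-1 value follows dosing. The article gives no interval from admission to randomisation, so day 1 could be pre-dose in some patients and post-dose in others. It cannot serve as a common baseline.

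What is at stake is the precision of one secondary comparison and the ability to report CRP change from baseline. The primary outcome, the safety data and the sample size are not affected.

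**Working it through.** The protocol states no figure on this point, so there is none to reproduce. The check has three parts.

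**1. Reading the schedule.**

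| Source | Time points |
|---|---|
| CRP outcome | days 1, 2, 3, 5, 7, 14, 21, 28 after admission |
| Albumin, procalcitonin, IL-6, neutrophils | days 0, 3, 5, 7, 14 (anchor of day 0 not stated) |
| Specimen collection {33} | admission, then 1, 3, 5, 7 days after admission |

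Because {33} names both an admission draw and a day-1 draw, day 1 after admission is not simply another label for the admission sample.

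**2. Does the missing baseline bias the comparison?** Allocation is random: "eligible participants will be randomised in a 1:1 ratio to either the treatment or control group". A simulation under no treatment effect used 20,000 trials, 124 patients per arm (the planned recruitment), normally distributed outcomes and an unadjusted t test at two-sided 0.05:

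| Baseline–outcome correlation ρ (assumed) | Type I error | Mean difference (SD units) |
|---|---|---|
| 0.3 | 5.2% | 0.0007 |
| 0.7 | 5.1% | 0.0012 |

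The error rate is nominal and the mean difference is essentially zero. The unadjusted test is valid.

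**3. What precision is left unused?** Adjusting for a baseline with correlation ρ to the outcome gives:

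- residual variance factor = 1 − ρ²
- standard-error factor = √(1 − ρ²)
- equivalent sample-size factor = 1/(1 − ρ²)
- power, for a comparison with 80% power unadjusted = Φ[(1.960 + 0.842)/√(1 − ρ²) − 1.960]

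The protocol gives no ρ, so a range is assumed:

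| ρ (assumed) | Variance factor | SE factor | Sample-size factor | Power (from 80%) |
|---|---|---|---|---|
| 0.3 | 0.91 | 0.95 | 1.10 | 84% |
| 0.5 | 0.75 | 0.87 | 1.33 | 90% |
| 0.6 | 0.64 | 0.80 | 1.56 | 94% |

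Worked line for ρ = 0.5: 1 − 0.25 = 0.75; √0.75 = 0.87; 1/0.75 = 1.33; 2.802/0.866 − 1.960 = 1.28, and Φ(1.28) = 0.90.

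Over a wider assumed range, ρ = 0.2 gives a variance factor of 0.96 (power 82%) and ρ = 0.7 gives 0.51 (power 97%). All these figures compare adjustment for day-0 CRP with no adjustment at all. The marginal gain over a model that already holds onset time or another day-0 marker would be smaller.

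**The case against.** The strongest reply is that an outcome list is not a data-collection schedule. Baseline is a covariate and need not be named among outcomes, and Table 2 may well schedule an admission CRP. This stands in part: nobody can say from the available text that no pre-treatment CRP is taken. But the same list does name day 0 for four laboratory markers, so the CRP item should be aligned with them and with Table 2 in any case.

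A reader might infer that cumulative CRP can never be corrected for starting inflammation. The documents do not support that. Serum and plasma from admission are stored, onset time must be known to establish eligibility, and day-0 procalcitonin, IL-6 and neutrophil count are available as partial substitutes.

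A reader might also infer that a chance imbalance in starting inflammation would be mistaken for a treatment effect. Chance imbalance is already allowed for in the error rate of the randomised comparison, as the simulation shows.

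Nor is CRP unlike every other marker. The contrast holds for the four laboratory markers; the pain and PASS scores are listed only as daily, with no day 0 named.

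Finally, adding day 0 alone would change nothing under an unadjusted test, and covariate adjustment is often left to a statistical analysis plan. That is fair. The absence of ANCOVA is not in itself a fault of the protocol; it is the second half of the remedy, without which the extra value has no use in the between-group test.

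**Conclusion.** The point holds as a minor one. As written, the cumulative CRP comparison uses no pre-treatment inflammation, although this varies with up to 72 h since onset, and change from baseline cannot be derived from the CRP values in the outcome list. The randomised comparison stays valid.

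The cost is precision: a residual variance factor of 0.91 to 0.64 forgone, or a standard error 5% to 20% larger than the adjusted one would be as a share of the unadjusted value. This rests on an assumed ρ of 0.3 to 0.6 and is an upper figure where onset time or other day-0 markers explain part of the same variation. CRP is one of about 20 secondary outcomes in a trial whose framework is described as exploratory, so the priority is low. The remedy is useful whatever Table 2 shows.

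**What to change.** 1. In the secondary outcome list, add a day-0 CRP defined as taken before the first study dose. State the anchor of day 0, and align the CRP numbering with Table 2 and with the other laboratory markers. Use the day-0 value as a covariate and keep it out of the cumulative total.
2. For the value itself, use the routine admission CRP. Where there is none, assay the stored admission sample for patients who agreed to use of their specimens. This also covers patients already enrolled, since recruitment began in August 2020. Check in each case that the sample precedes the first dose.
3. State in the analysis text that cumulative CRP is compared by ANCOVA on the log scale, with log day-0 CRP and hours from onset to randomisation as covariates. The effect is then reported as a ratio of geometric means.

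Cost: at most one assay for each of the 248 planned patients, so at most 248 assays, with no new venepuncture, plus a few lines in the outcome and analysis wording.

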### Participant timeline {13}

The participant timeline is shown in Table 2.

**Table 2 Tab2:**
[figure not shown]
Study schedule of the CAP trial

*CQCQD* chaiqin chengqi decoction, *EQ-5D-5L* five-level EuroQol five-dimensional questionnaire, *CRP* C-reactive protein

### Sample size {14}

The sample size calculation was based on the following assumptions: a reduction in duration of respiratory failure of 2 days in the treatment group, and a standard deviation of 4.5 days for each group [17, 29]. Assuming that the significance level is 0.05 and the study power is 0.8 (two-sided *α* = 0.05, *β* = 0.2), we projected a sample size of 111 patients in each group using Power Analysis & Sample Size software (PASS statistic software, version 11.0.7, NCSS). Considering a 10% dropout rate, a total of 248 patients will be recruited in this trial with 124 patients for each group.

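### The 111 patients per group is not reproduced by a t test on the stated inputs, which need 81; at 111 per group the power is about 91%, not 80%

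*Protocol article*

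**What the plan says.** The section Sample size {14} of the protocol article sets out the assumptions as "a reduction in duration of respiratory failure of 2 days in the treatment group, and a standard deviation of 4.5 days for each group". The error rates are given as "two-sided *α* = 0.05, *β* = 0.2". The result is that "we projected a sample size of 111 patients in each group", obtained with a named commercial sample-size package. Dropout is then added: "Considering a 10% dropout rate, a total of 248 patients will be recruited in this trial with 124 patients for each group".

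Allocation is equal (Sequence generation {16a}: "eligible participants will be randomised in a 1:1 ratio to either the treatment or control group"). The sample size section names no test and mentions no variance inflation or non-parametric adjustment. The section Statistical methods for primary and secondary outcomes {20a} plans a t test for continuous variables, or a Mann–Whitney test where the distribution is not normal. The section Interim analyses {21b} says that none is planned, so no alpha spending enters the calculation.

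**The concern.** The article prints all the inputs of a two-group comparison of means together with the answer, and the answer is 30 per group larger than those inputs require (111 − 81). That is too large a gap for rounding or for a difference between software packages.

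The paragraph is where a reader learns which effect the trial was built to detect, and with what power. As printed it allows incompatible readings: a 2-day effect at about 91% power, or an effect of about 1.7 days (or an SD of about 5.3 days) at 80%. Anyone setting a null primary result against the design target would not know which target applied.

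**Working it through.** **Inputs.** All are from Sample size {14}, except the allocation ratio, which is from Sequence generation {16a}: difference 2 days; SD 4.5 days in each group; two-sided alpha 0.05; power 0.80; allocation 1:1; dropout 10%. The standardised difference is d = 2/4.5 = 0.444.

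**1. The dropout step reproduces.** 111/(1 − 0.10) = 123.3, rounded up to 124 per group and 248 in total. Dropout is added after the 111, so it does not explain the 111.

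**2. The 111 does not reproduce.**
- Normal approximation: n = 2 × (1.960 + 0.842)² × 4.5²/2² = 79.5, so 80 per group.
- Two-sample t test (noncentral t): n = 80.4, so 81 per group.
- After 10% dropout: 81/0.9 = 90 per group, 180 in total. The plan has 248, which is 68 more (68/180 = 38%).

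**3. Power at 111 per group on the stated inputs.**
- Normal approximation: the standard error is 4.5 × √(2/111) = 0.604; 2/0.604 − 1.960 = 1.351; power 0.912.
- t test: 0.909.

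**4. Usual rank-test adjustments.** These divide the t-test size by the relative efficiency of the Mann–Whitney test under a location shift.
- Normal data (efficiency 3/π): 80.4 × π/3 = 84.2, so 85 per group.
- Lowest efficiency for a continuous location shift (0.864): 80.4/0.864 = 93.1, so 94 per group.
- Power at 111 per group under these two adjustments is 0.896 and 0.865.

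**5. What would give about 111.** Each line changes one or more stated inputs.

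| Change | t test, per group |
|---|---|
| SD about 5.3 days, rest as stated | about 111 |
| Difference about 1.7 days, rest as stated | 111 |
| 90% power, two-sided | 108 (113 for the rank test under normality) |
| One-sided alpha 0.05, 95% power | 111 |
| One-sided alpha 0.05, 80% power | 64 |

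The first two lines follow from solving for 80% power at 111 per group: d = 0.378, so the difference is 0.378 × 4.5 = 1.70 days, or the SD is 2/0.378 = 5.3 days. These are back-solved values. They are not evidence of what was entered.

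**The case against.** The strongest objection concerns the rank test. The efficiency bound of 0.864 applies to continuous outcomes under a pure location shift. The primary outcome is a number of days of respiratory failure within 28 days, and entry requires predicted moderately severe or severe disease, not respiratory failure. Zero durations and ties are therefore likely, and a treatment that shortens a non-negative duration does not act as a shift. A simulation shows that this can matter. It used zero-inflated gamma durations rounded to days, with 55% zeros in both arms, means of 4 and 2 days and an SD of 4.5 days in each arm. Mann–Whitney power was about 0.69 at 81 per group and about 0.82 at 111. The means and the zero fraction are assumptions; the protocol gives neither, and most other settings tried gave power above 0.86 at 111.

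This part of the objection stands. A reader might infer that at least one printed figure cannot be what was entered in the software, or that no rank-based calculation could lead to 111. The document does not support either inference: all the printed figures could be as entered, with the procedure left unreported. But the sample size section describes no such calculation, so the objection does not show that the trial was sized this way, and 111 remains unexplained.

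It can also be said that the discrepancy is harmless, because the trial is larger than its stated target requires, calls itself exploratory and started recruiting in August 2020. A completed trial will also be read mainly from its estimate and confidence interval. That lowers the consequence. It does not make the printed figures agree, and the reassurance about size holds only if 2 days and 4.5 days are the true inputs.

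**Conclusion.** The point holds as an inconsistency within one paragraph. For a two-sample t test the stated inputs give 81 per group, not 111, and 111 per group gives about 91% power, not 80%. The standard location-shift adjustments for a rank test do not close the gap. Either the difference, SD, power, sidedness or N is misreported, or an unstated test or adjustment was used; the article does not allow a choice between these.

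A reader might go further and conclude either that the trial is underpowered or that it surely has power to spare. Neither follows. On the printed inputs the discrepancy is conservative, by 68 patients in total. If the calculation in fact used an SD of about 5.3 days or a difference of about 1.7 days, 111 per group is just enough for 80% and there is no surplus.

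The figure of 91% rests on the t test, a common SD of 4.5 days, a true difference of 2 days and 111 evaluable patients per group. The dropout calculation is correct, and the inconsistency has no bearing on the type I error or on the choice of analysis.

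**What to change.** Retrieve the original software output and correct the sample size paragraph in one of two ways:

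- If 2 days and SD 4.5 days were the inputs to a t test, keep them and restate the power as about 91% at 111 per group.
- If something else was entered, print the SD, difference, sidedness or power actually used.

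In either case, name the test, and any non-parametric or other adjustment, on which the 111 rests. Keep the enrolment target of 248. The cost is a corrected sentence or two in the protocol, with no change to recruitment or conduct.

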### Recruitment {15}

Patients admitted to the Emergency Department of West China Hospital will be primarily screened via the symptoms of abdominal pain and onset time by research nurses. Patients with a diagnosis of AP will be admitted to Pancreatitis Centre Ward for further recruitment.

## Assignment of interventions: allocation

### Sequence generation {16a}

After the completion of screening measurements and the acquisition of signed consent, eligible participants will be randomised in a 1:1 ratio to either the treatment or control group. The randomisation code will be automatically created by computer using Analytics Software & Solutions software (SAS, version 9.3, SAS Institute Inc, USA).

### Concealment mechanism {16b}

Patients will be randomised using sequentially numbered, opaque sealed envelopes, which is the most accessible and straightforward method of maintaining allocation concealment. A group of independent assessors will interview the patients and perform the screening.

### Implementation {16c}

Statistician ([name]) generated the allocation sequence. Research assistants will continue the enrolment process by screening eligible patients according to the inclusion and exclusion criteria and assigning participants to interventions.

## Assignment of interventions: blinding

### Who will be blinded {17a}

All the patients, researchers, and statisticians in this clinical study will be blinded to the treatment assignment and unaware of the actual medications.

### Procedure for unblinding if needed {17b}

The study blinding will only be broken in a medical emergency when the treating physician believes that the administration of the study drug is associated with the emergency.

## Data collect and management

### Plans for assessment and collection of outcomes {18a}

According to the study schedule shown in Table 2, data will be collected during the index admission and 26 weeks after enrolment. If a participant wishes to discontinue the study drug or the treating physician believes a participant should discontinue the study drug due to medical conditions, the investigator will communicate with the participant and the treating physician to obtain the reasons and record in CRF. Further follow-up will still be performed unless the participant withdraws from the trial.

### Plans to promote participant retention and complete follow-up {18b}

Participants are encouraged to visit the researchers in outpatients on weeks 6, 12, and 26 after enrolment, but they will decide a relatively flexible visiting time or follow-up via telephone. During the follow-up period, participants will receive personalised telephone and online counselling with doctors so that they will receive qualified medical care by the research group. They can emergently contact the researcher ([name]) if they have discomfort. Incentives to promote adherence will also be provided (e.g. free registration fees, during follow-up transportation allowances, admission priority due to recurrence or complications of pancreatitis).

### Data management {19}

The researchers involved will receive restricted training to ensure that the study process is detailed. Data collection will use a CRF and include source-verifiable data from patient records. CRF will be anonymised and contain no individual patient-identifiable information. Paper copies of the CRF will be stored in a locked cabinet in the Chief Investigator’s office in West China Hospital. All data will be input by the primary investigator or nominated investigators approved by the primary investigator, and a double check will be performed by the research coordinator.

### Confidentiality {27}

At the time of recruitment, an unrelated sequence of characters will be used to replace the participant’s identifiable information. The data will be stored in the Pancreatitis Centre Information Records Office and will only be accessible to researchers, data monitors, and the BREC of West China Hospital.

